### Design

Patients with diagnosed SCAP are randomized to the following four groups at a 1:1:1:1 ratio:Group 1 (control group): standard ICU patient care+100ml of normal saline once a day for 5 days. Standard ICU patient care involves ventilatory, hemodynamic, antimicrobial, nutritional, and other supports according to the guidelines for the diagnosis and treatment of community-acquired pneumonia in Chinese adults (2016 Edition). At present, there are no relevant guidelines to recommend methylprednisolone as a therapeutic drug for SCAP, which indicates that a consensus has not been reached and disputes still exist. Thus the placebo control group is still needed.Group 2: standard ICU patient care+40mg of methylprednisolone (dissolved in normal saline with a final volume of 100ml) once a day for 5 days.Group 3: standard ICU patient care+80mg of methylprednisolone (dissolved in normal saline with a final volume of 100ml) once a day for 5 days.Group 4: standard ICU patient care+120mg of methylprednisolone (dissolved in normal saline with a final volume of 100ml) once a day for 5 days.

Researchers will explain the research procedures in detail to the subject or agent to obtain the informed consent and will evaluate intervention adherence during each visit. If a scheduled visit is delayed or canceled, the research team will contact the subject immediately. No concomitant care or intervention is prohibited during the study. The trial is planned to be followed up for 28 days after randomization. The schedule of enrolment, interventions, and assessments is shown in Fig. 1.

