### Primary outcome

PaO_2_/FiO_2_ ratio at day 5 following randomization

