### Sample size

On the basis of previous study [12], it is calculated by Tukey-Kramer test that 220 participants will be required (55 in each group) to detect a difference of 50mmHg in the PaO_2_/FiO_2_ ratio between groups, assuming a standard deviation (SD) of 50mmHg in the control group (80% power, *α*= 0.05). If the follow-up rate is assumed to be 90%, 244 participants with 61 in each group will be needed. Sample size calculation was performed by PASS 11 software.

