### Statistical analysis

We will show *n* (%) for categorical variables and median (interquartile range) for continuous variables with non-normal distribution or mean (SD) for those with normal distribution. Data for the primary and secondary outcome will be analyzed on intention-to-treat analysis, and missing data will be handled by multiple imputation method. If variances are equal, comparison of continuous variables will be evaluated by one-way analysis of variance, followed by the least significance difference procedure; otherwise, the Games-Howell procedure will be followed. The *χ*^2^ test followed by the Bonferroni method will be used to evaluate the comparison of categorical variables. Subgroup analysis will be used when appropriate. SPSS 18.0 software will be employed for statistical analysis. Significance level is set at 0.05.

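### Under equal variances the primary pairwise comparisons use LSD, which holds familywise error at 5% only if all four arms are equal and departs from the Tukey-Kramer basis of the sample size

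*Protocol article*

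**What the plan says.** The primary outcome is continuous: the PaO2/FiO2 "ratio at day 5 following randomization" (Protocol article, Primary outcome). The Design section has four arms: "Patients with diagnosed SCAP are randomized to the following four groups at a 1:1:1:1 ratio". That gives six pairs, three of a dose against placebo and three of one dose against another.

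The Statistical analysis section states that, if variances are equal, "comparison of continuous variables will be evaluated by one-way analysis of variance, followed by the least significance difference procedure". If they are not, Games-Howell is used. For categorical outcomes, the chi-square "test followed by the Bonferroni method will be used to evaluate the comparison of categorical variables". The section adds "Significance level is set at 0.05". It gives no primary contrast and no testing order that would narrow the family of comparisons.

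The Sample size section rests on a different procedure: "it is calculated by Tukey-Kramer test that 220 participants will be required (55 in each group"), "to detect a difference of 50mmHg" between groups, "assuming a standard deviation (SD) of 50mmHg in the control group", with 80% power and alpha 0.05. Tukey-Kramer does not appear in the Statistical analysis section.

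**The concern.** LSD compares each pair at an unadjusted 5%. Its only protection is the preceding ANOVA, and that works only when all four means are equal. Once one arm truly differs, the ANOVA tends to be significant for that reason, and the pairs that are truly equal are then tested without protection.

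This bears on the trial's own question. The Background treats the adjuvant effect of methylprednisolone as fairly well settled and dose dependence as the open issue; the Discussion hopes to identify a best dose. A drug that works about equally well at all three doses is therefore a plausible truth, and it is the case in which LSD is most likely to report a dose difference that does not exist.

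The article also contradicts itself. Its sample size basis, its unequal-variance branch and its categorical analysis all adjust for multiple comparisons; the equal-variance branch for continuous outcomes does not.

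**Working it through.** **Inputs.** Four arms (Design); 55 per group, difference 50 mmHg, SD 50 mmHg, 80% power, alpha 0.05 (Sample size). Assumptions: two-sided tests, and the SD, which is stated for the control group only, taken as common to all arms.

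**The plan's own figure.** Per-pair Tukey power is P(t′ > c), where t′ is noncentral t with 4(n − 1) degrees of freedom and noncentrality (δ/SD)·√(n/2), and c = q(0.95; 4, df)/√2. On the stated inputs, 80% power needs 25 per group, so 55 is not reproduced. It gives about 80% only if the SD is about 76 mmHg. That is a separate matter, but it affects the cost of the fix, so both SDs are carried below.

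**Critical values at n = 55 (df = 4 × 54 = 216).**
- LSD: t = 1.97. Tukey-Kramer: 2.59.
- Standard error of a difference: 50 × √(2/55) = 9.53 mmHg.
- A pair is declared different at 1.97 × 9.53 = 18.8 mmHg with LSD and at 2.59 × 9.53 = 24.7 mmHg with Tukey-Kramer.

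**Familywise error by simulation** (200,000 to 400,000 trials per pattern; LSD run only after a significant F). Means are in the order placebo, 40, 80, 120 mg, in mmHg relative to placebo. Error is the chance of at least one false positive among truly equal pairs.

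| True means | F significant | LSD, all null pairs | LSD, dose-versus-dose null pairs | Tukey-Kramer, all null pairs |
|---|---|---|---|---|
| 0, 0, 0, 0 | 5.0% | 5.0% (20.1% without the F gate) | at most 5.0% | 5.0% |
| 0, 50, 50, 50 | over 99.9% | 12.2% | 12.2% | 2.8% |
| 0, 30, 30, 30 | 91% | 12.1% | 12.1% | 2.8% |
| 0, 20, 20, 20 | 55% | 10.7% | 10.7% | about 2.8% |
| 0, 15, 15, 15 | 33% | 8.6% | 8.6% | about 2.8% |
| 0, 0, 50, 50 | about 100% | 9.6–9.8% | about 5% | 2.0–2.1% |
| 0, 0, 0, 50 | over 99.9% | 12.2% | about 5% | 2.8% |

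In rows two to five every null pair is dose-versus-dose, so the two LSD columns agree. In the last two rows only one null pair is dose-versus-dose; the others involve placebo. A hand check on the two-pairs row: two nearly independent null tests at 5% give 1 − 0.95² = 9.75%.

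**Cost in power at n = 55, per pair.**
- 50 mmHg, SD 50: noncentrality 1.0 × √27.5 = 5.24; Tukey-Kramer 99.6%, LSD 99.9%.
- 30 mmHg, SD 50: noncentrality 0.6 × √27.5 = 3.15; Tukey-Kramer 71%, LSD 88%.
- 50 mmHg, SD 76 (assumed): noncentrality 0.658 × √27.5 = 3.45; Tukey-Kramer 80%, LSD 93%.

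**The case against.** The strongest reply is that LSD here follows an ANOVA, so the global test holds 5% and a completely inert drug produces false findings no more often than stated. That stands. A reader might infer from the choice of LSD that there is no error control at all; the text does not support this, since the natural reading of its wording is a gated procedure. What is missing is control when some arms differ and others do not.

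Other limits also stand:

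- A reader might infer that all six pairs are dose comparisons, or that every inflated figure is a false difference between doses. Three pairs are against placebo. In the two patterns where placebo equals at least one dose, dose-versus-dose error stays near 5% and the excess comes from counting all null pairs.
- The 12% is close to the maximum. With smaller true effects the ANOVA is significant less often and the error falls.
- The primary outcome need not go through LSD. If variances are judged unequal, Games-Howell applies and adjusts. The article states an SD for the control group only, so it does not show which branch will be used.
- A reader might infer that the mismatch leaves the trial short of patients. It does not: sizing on the stricter procedure and analysing with the more lenient one errs on the safe side for power.
- Tukey-Kramer is not the only valid remedy. It is conservative when only some arms are equal (2.0% to 2.8%), and another procedure with strong familywise control, such as ordered contrasts, would serve if both sections used it.

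None of this removes the point. LSD is a stated choice, not a detail left to an analysis plan that is not shown, and it conflicts with the article's own planning basis.

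**Conclusion.** The point holds for the equal-variance branch. There, LSD after ANOVA keeps familywise error at 5% only when all four arms are equal. In the case that matters most for this trial, three equally effective doses that differ from placebo, the chance of at least one false dose difference on the primary outcome is about 8.6% at 15 mmHg, 10.7% at 20 mmHg and 12% at 30 to 50 mmHg, against a stated level of 5%. The figures assume 55 analysed patients per group, a common SD of 50 mmHg, normal data and LSD run only after a significant ANOVA; without that gate the error is already 20.1% when nothing differs. Because the other branch adjusts, error control on the primary outcome depends on a variance check. The rule is wrong as written, inconsistent with the Sample size section, and cheap to correct.

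**What to change.** In the Statistical analysis section, replace LSD with Tukey-Kramer for pairwise comparisons under equal variances, so that it matches the Sample size section. Keep Games-Howell for unequal variances. Report confidence intervals adjusted by the same procedure. Make the change before unblinding.

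The edit is one sentence. The price is the higher critical value: negligible for the planned 50 mmHg at the stated SD, but a real loss of 17 percentage points for a 30 mmHg difference (88% − 71%). If the SD were about 76 mmHg, power for 50 mmHg would fall by 13 points (93% − 80%) but still meet the 80% target; with a larger SD it would not. On the stated inputs no patients need to be added.

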Glucocorticoid is widely used in the treatment of severe infection because of its anti-inflammatory effect. Many evidence-based studies have reported that early application of glucocorticoid can affect the development of SCAP, promote disease recovery, and may reduce the mortality [5–8]. However, there is no consensus on the specific use of glucocorticoid in SCAP (such as type, dose, course of treatment, etc.) [4, 9, 10], and different methods of application bring diverse clinical outcomes [11–19]. Mikami et al. [13] found that administration of 40 mg of prednisolone for 3 days in patients with SCAP could promote resolution of clinical symptoms and reduce the duration of intravenous antibiotic therapy. Li et al. [16] recruited patients with SCAP complicated with septic shock to receive 80 mg of methylprednisolone or placebo for 3 days. The results showed that methylprednisolone could significantly improve oxygenation index, reduce serum C-reactive protein (CRP) level, and shorten the time of temperature recovery, duration of vasopressors use, and hospital stay, without increasing the incidence of adverse events. The findings of Li et al. were similar to the reports from another trial [18] that adopted 120mg of methylprednisolone to treat with patients with SCAP for 7 days. However, Zhao et al. [19] observed that although the improved oxygenation and the decreased levels of CRP and angiotensin II were detected after a 7-day therapy with 80–160mg of methylprednisolone, the length of hospital stay and mortality did not change, and the incidence of superinfection was significantly increased.

To sum up, the adjuvant effect of methylprednisolone in SCAP tends to be clear. However, the specific use of methylprednisolone has not yet formed a consensus, which needs further clinical demonstration. It is not clear whether the clinical efficacy of methylprednisolone in SCAP is dose-dependent, and how to balance the best efficacy with the least complications. As far as we know, no such research has been carried out.

The purpose of this superiority trial is to evaluate the efficacy and safety of different doses of methylprednisolone in the adjuvant treatment for patients with SCAP.

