### Secondary outcomes

Twenty-eight-day mortality (death proportion within 28 days of randomization)Sixty-day mortality (death proportion within 60 days of randomization)Ventilator-free days at 28 days (the number of days free from mechanical ventilator support in the first 28 days following randomization)Mechanical ventilation duration at 28 days (the number of days during mechanical ventilation within 28 days of randomization).Endotracheal intubation rate (the proportion of patients requiring endotracheal intubation within 28 days of randomization)Time for temperature recovery (the number of days required for body temperature to return to normal)Duration of vasopressors use (the number of days required for continuous use of vasopressors)Serum CRP and interleukin-6 level at day 5 following randomizationHospital stayFrequency of nosocomial infections (the number of ventilator-associated pneumonia, blood stream infection or candidemia within 28 days of randomization)Gastrointestinal hemorrhage (the proportion of gastrointestinal bleeding patients requiring additional medication, blood transfusion, or surgical intervention within 28 days of randomization)Hyperglycemia (the proportion of patients with hyperglycemia requiring insulin injection within 28 days of randomization)

All adverse events and other unintended effects of trial interventions or trial conduct will be collected and documented, regardless of severity. Participants who suffer harm from these events will be compensated accordingly.

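### The Bonferroni step for all categorical outcomes also covers the harms defined as proportions, and at 61 per arm it makes a doubling of an uncommon harm still harder to detect

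*Protocol article*

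**What the plan says.** The Background of the protocol article asks "how to balance the best efficacy with the least complications" and continues: "The purpose of this superiority trial is to evaluate the efficacy and safety of different doses of methylprednisolone". Safety by dose is therefore an aim in its own right.

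Under Secondary outcomes, two harms are proportions of patients. One is "Gastrointestinal hemorrhage (the proportion of gastrointestinal bleeding patients requiring additional medication, blood transfusion, or surgical intervention within 28 days of randomization"; the other is hyperglycemia needing insulin within 28 days. Nosocomial infection is defined as a number of infections, so it is categorical only if it is analysed by patient.

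Under Statistical analysis, the one comparison named for categorical outcomes is a chi-square "test followed by the Bonferroni method will be used to evaluate the comparison of categorical variables", with "Significance level is set at 0.05". The number of comparisons is not given. Continuous outcomes, including the primary, are compared by analysis of variance. If variances are equal, this is followed by the least significant difference procedure, which does not adjust the pairwise tests; otherwise Games-Howell follows.

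Under Sample size, "220 participants will be required (55 in each group") for a PaO2/FiO2 difference, and after allowance for loss "244 participants with 61 in each group will be needed". No harm rate enters the calculation.

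**The concern.** A Bonferroni correction protects against declaring a difference that is not there. For an efficacy claim that is the costly error. For a harm the costly error is usually the opposite one, overlooking a real increase, and the correction makes it more likely.

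With equal variances, the stated rules leave the pairwise tests of the primary outcome unadjusted and tighten those of bleeding and hyperglycemia. In a trial meant to weigh benefit against complications dose by dose, the strictness sits on the wrong side. At stake is how much the harm comparisons can tell a reader. For an uncommon complication, a non-significant result would be the likely outcome even if the highest dose doubled it.

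**Working it through.** **Inputs from the article.** Four arms allocated 1:1:1:1; 55 per arm before and 61 per arm after allowance for loss; overall level 0.05; chi-square then Bonferroni.

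**The plan's own figure.** "If the follow-up rate is assumed to be 90"%, then 55/0.9 = 61.1 and 220/0.9 = 244.4, which agrees with 61 per arm and 244 in total. The 55 itself is not reproduced: a difference of 50 and an SD of 50 mmHg with Tukey-Kramer need about 24 per group for one given pair. That is a separate matter. The check below takes the planned 61.

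**Assumptions.**
- The article gives no control rate for any harm, so a range is used.
- The rate rises in equal steps from saline to 120 mg.
- Bonferroni covers either all six pairs (0.05/6 = 0.0083) or the three dose-saline pairs (0.05/3 = 0.0167).

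**Closed-form check of one pair, 10% against 20%, n = 61.** Power = Φ[(d − z·SE0)/SE1], where:
- d = 0.10
- SE0 = √(2 × 0.15 × 0.85/61) = 0.0647
- SE1 = √((0.10 × 0.90 + 0.20 × 0.80)/61) = 0.0640

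Results:
- Six pairs, z = 2.638: Φ[(0.10 − 0.1706)/0.0640] = Φ(−1.10) = 13.5%
- Three pairs, z = 2.394: Φ[(0.10 − 0.1548)/0.0640] = Φ(−0.86) = about 20%
- No correction, z = 1.960: Φ[(0.10 − 0.1267)/0.0640] = Φ(−0.42) = 34%

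**Simulation of the stated procedure.** A Bonferroni detection requires the four-arm chi-square to give p < 0.05, and saline against 120 mg to be significant at the corrected level with more events on 120 mg. The last column is the pairwise test at 0.05 alone. Chance of missing a doubling, 61 per arm:

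| Saline to 120 mg (assumed) | Six pairs | Three pairs | Uncorrected pair |
|---|---|---|---|
| 10 to 20% | 88% | 84% | 67% |
| 15 to 30% | 75% | 71% | 48% |
| 20 to 40% | 59% | 54% | 32% |
| 25 to 50% | 41% | 35% | 18% |
| 30 to 60% | 24% | 20% | 7% |

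At 40 to 80% with six pairs the miss rate is about 2%. With 55 per arm, 15 to 30% is missed 79% of the time with six pairs and 52% uncorrected.

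The last column drops the four-arm test as well as the correction. That gate adds only about one point under six pairs: without it the first three misses are about 87%, 74% and 58%. Nearly all of the gap between the six-pair and uncorrected columns therefore remains when both tests are run without the gate.

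**Where the balance turns.** For a single pair, power for a doubling passes 50% at a control rate of about 23% (six pairs), 20% (three pairs) or 15% (uncorrected).

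**What intervals would show.** The 95% half-width for equal rates is 1.96 × √(2p(1 − p)/61), which is 10.6 points at p = 10% and 14.2 points at p = 20%.

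**The case against.** Chi-square followed by Bonferroni is a standard procedure for proportions in four arms. The article condenses a fuller protocol, and intervals for harms may be in an analysis plan that is not shown. Their absence is not the point here. The point is that the article fixes a rule and that the rule takes in the harms.

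Four stronger readings are tempting, and the document does not support them.

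- **A doubling would usually be missed, whatever the harm.** No harm rates are given, and the table reverses from about 25% upward. The four-arm test can also signal: at a 20% control rate its power is about 72% if only the top dose doubles the rate and 69% if all doses do, though it does not say which dose is responsible.
- **Bonferroni is the cause.** For uncommon harms arm size matters more: at 10 to 20% the uncorrected test still misses 67%. The correction adds about 20 points to that.
- **A non-significant harm will be read as safe, and a dose named optimal on that basis.** A reader might infer this, since the Background describes earlier trials as having or not having increased adverse events. No sentence sets such a rule.
- **This is the only information on safety.** Counts and percentages will be shown by arm, all adverse events are collected, and a data monitoring committee reviews data. None of these sets how doses are compared on a harm, but the harm data would not be empty.

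Whether to correct harm comparisons for multiplicity is partly a matter of judgement, and dropping the correction raises false alarms. That stands as a cost. A pre-set margin for claiming no increase is also open to debate, because the document offers no rate or margin to base one on; none is asked for here.

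**Conclusion.** The point holds in a limited form. The stated rule applies a correction against false positives to harms defined as proportions, in a trial that has safety by dose as an aim and is sized on oxygenation alone. For control rates of 10 to 20%, a doubling at the highest dose is missed about 59 to 88% of the time with six pairs and 54 to 84% with three, against 32 to 67% for an uncorrected pairwise test. These figures rest on assumed rates, a graded increase and 61 analysed per arm; with 55 they are higher. For common harms the concern largely disappears. Arm size sets most of the limit and the correction worsens it, which is a reason to estimate harms rather than rely on corrected tests.

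**What to change.** In Statistical analysis, restrict the Bonferroni step to the categorical efficacy outcomes. For gastrointestinal hemorrhage, hyperglycemia, nosocomial infection (if analysed by patient) and other adverse events, report each dose against saline as a risk difference with an unadjusted two-sided 95% confidence interval. Add a sentence that a non-significant difference in a harm is not evidence of safety.

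The cost is a change of wording and a few table columns; no patients or data are added. The downside is more false alarms: with three unadjusted dose-saline intervals per harm, the chance that at least one excludes zero when no dose differs can reach at most about 3 × 5% = 15%. The intervals will also be wide, which reflects the arm size and should be visible.

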### Data collection and management

Our study will use printed case report form (CRF) to collect the original data and will establish an electronic clinical research database to record all the information from CRF. We will use Epidata 3.1 software for dual data input and data proofreading. During the study, medical staff who did not participate in the study will supervise the trial. They will access the database to monitor all aspects of the study, including adherence to the study protocol, protection of participants, and accuracy of study data.

### Trial supervision

The data monitoring committee is established by the medical ethics committee and the Department of Science and Education of Shengli Oilfield Central hospital. According to the data review during the trial, the committee can make suggestions such as modifying the protocol and continuing or stopping the trial. Any important protocol modifications will be communicated to the relevant parties by the committee to ensure the consistency of the protocol. The datasets analyzed during the present study are available from the corresponding author on reasonable request.

